| Objectives, Specific Aims and Rationale Overall aim  To investigate ethnic differences in prescribing for type 2 diabetes in UK primary care.  Objectives  For people of European, South Asian and African Caribbean origin, ethnic differences in the following will be investigated:   1. Proportions of people with: a) incident hypertension started on antihypertensives and b) an elevated 10 year CVD risk score (according to QRISK, ASSIGN, JBS2, Framingham or unspecified risk-estimating equations (26)) being commenced on statin treatment. 2. Time to initiation of first-line anti-diabetic/ antihypertensive/lipid-lowering medication 3. Choice of anti-diabetic (first- to third-line), antihypertensive and lipid-lowering medication 4. Doses used for each anti-diabetic, antihypertensive and lipid-lowering medication 5. Monitoring rate after medication commencement 6. Time to medication intensification (up-titration, addition or switching) after detection of sub-optimal control of diabetes, hypertension or blood lipids   Additionally, we will examine potential confounding or mediating role/s of:   1. Smoking, BMI, deprivation, polypharmacy, multi-morbidity, drug adherence (for objectives v) and vi)), patient engagement with healthcare, diabetes duration and HbA1c (in people with diabetes).   Null hypotheses   1. No ethnic difference in proportions of people started on a) antihypertensives or b) statin treatment will be detected. 2. No ethnic difference in time to initiation of first-line anti-diabetic, antihypertensive or lipid-lowering medication will be detected. 3. Regarding choice of medication: 4. No ethnic difference in the proportions of people prescribed metformin as first-line, or sulphonylureas, DPP4-inhibitors, thiazolidinediones, SGLT2 inhibitors, GLP1 agonists or insulin as second- or third-line diabetes treatment will be observed. 5. No ethnic difference in the proportions of people prescribed ACE inhibitors/ angiotensin-receptor blockers, calcium-channel blockers or thiazide diuretics for hypertension will be observed. 6. No ethnic difference in the proportions of people with ≥10% cardiovascular disease risk who are prescribed lipid-lowering medication will be observed. 7. No ethnic difference in the proportions prescribed the maximum dose of anti-diabetic, antihypertensive or lipid-lowering medication will be observed, and the modal dose for each class will not differ by ethnicity. 8. No ethnic difference in the monitoring rates of anti-diabetic, antihypertensive or lipid-lowering medication will be observed. 9. No ethnic difference in time to treatment intensification (after the detection of sub-optimal control) of anti-diabetic, antihypertensive or lipid-lowering medication will be observed. 10. Associations between ethnicity and prescribing will not be confounded or mediated by smoking, BMI, deprivation, polypharmacy, multi-morbidity, drug adherence, patient engagement, diabetes duration or HbA1c (in people with diabetes).   Rationale  Research indicates that control of diabetes and its allied cardiovascular risk factors is poorer in UK’s minority ethnic groups than in the background white population. Crucially, these discrepancies are likely to contribute to higher rates of heart disease and stroke, in people with and without diabetes, seen in these groups. By examining the associations above, this study seeks to determine whether ethnic differences in prescribing for people with and without diabetes are present, and explanations for them.  It is important to compare prescribing in people with and without diabetes for each ethnic group. Our previous work suggests that diabetes is a much more potent CVD risk factor in people of South Asian and African Caribbean-origin than those of European-origin, and differential prescribing of statins and anti-hypertensives in those with vs. without diabetes is a possible explanation for this.  If ethnic inequalities in prescribing are present, their identification may influence future prescribing recommendations and thus eventually lessen the personal and societal burden of diabetes and cardiovascular disease complications in ethnic minority groups. |

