| Feasibility counts The primary analysis will be using data from CPRD alone (see section M for sensitivity analyses). Ethnicity recording for active patients is approximately 50% (17, 18). The ethnic breakdown is similar to that of the UK census 2011(20).  From 2000-2017, ≈280K patients initiated first-line and ≈80K second-line treatment for type 2 diabetes in CPRD (8). If 50% of these people had ethnicity codes present in their record, this would correspond to ≈140K starting first-line and ≈40K starting second line treatment. Using the 2011 census to calculate proportions, this would equate to ≈120.4K Europeans, ≈10.5K South Asians and ≈4.6K African Caribbeans initiating first-line treatment and 34.4K, 3.0K and 1.3K respectively starting second-line treatment. These are conservative estimates given the over-representation of ethnic minorities in the diabetic population.  Approximately 77% of the people with diabetes initiating first-line treatments are likely to be on antihypertensives (19), giving numbers for antihypertensive analyses of ≈92.7K Europeans, ≈8.1K South Asians, ≈3.5K African Caribbeans. Previous work in CPRD shows that ≈64% of people with type 2 diabetes receive statins (19), which will yield numbers for the lipid-lowering medication analyses of ≈77.1K Europeans, ≈6.7K South Asians and ≈2.9K African Caribbeans.  For people without diabetes, we expect approximately 219K people to initiate antihypertensive treatment over a similar study period to our own (20), equating to at least 94K Europeans, 6K South Asians and 3K African Caribbeans, once multipliers for ethnicity recording and the 2011 Census ethnicity breakdown are applied. From Chidwick et al (21), 113,035 people over 40 without a prior history of CVD had a high CVD risk score recorded between 2005-2013. Assuming 50% of these people had ethnicity recorded, and proportions by ethnicity are as per the 2011 census, this equates to approximately 49K Europeans, 3K South Asians and 2K African Caribbeans. |

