| Sample size considerations Anti-diabetic analyses  Sample sizes as per “feasibility counts” section, see table 1(below) for detectable differences in ethnic difference effect sizes. Corresponding to objective i), the proportion prescribed an anti-diabetic at 1 year post-diagnosis (42%) is taken from Sinclair et al (22) (detectable differences calculated using stpower cox command in Stata). Corresponding to objective ii), proportions prescribed metformin as first-line (73%) and a sulphonylurea as second line treatment (87%) are taken from Wilkinson et al (8) (power twoproportions command). Corresponding to objectives iv) and v), mean monitoring rate (2.45 times per year [extrapolated], assuming a SD of 2) (power twomeans command) and probability of treatment intensification at 1 year (24%) are taken from Khunti et al (23) (stpower cox command).  **Table 1. Detectable ethnic differences in outcomes.**   \| **Outcome** \| **Exposure (ethnicity): N vs. N** \| **Detectable ethnic difference effect sizes at α=0.05, β=0.90** \| \| --- \| --- \| --- \| \| Time from diagnosis to first anti-diabetic prescription \| South Asians vs. Europeans:  10.5K vs. 120.4K \| HR: 1.03 \| \| African Caribbeans vs. Europeans:  4.6K vs. 120.4K \| HR: 1.03 \| \| % prescribed metformin first-line \| South Asians vs. Europeans:  10.5K vs. 120.4K \| Difference in proportions: 1.4% \| \| African Caribbeans vs. Europeans:  4.6K vs. 120.4K \| Difference in proportions: 2.1% \| \| % prescribed sulphonylurea second-line \| South Asians vs. Europeans:  3.0K vs. 34.4K \| Difference in proportions: 2.0% \| \| African Caribbeans vs. Europeans:  1.3K vs. 34.4K \| Difference in proportions: 2.9% \| \| Mean monitoring rate, measurements per person year at risk \| South Asians vs. Europeans:  10.5K vs. 120.4K \| Rate difference: 0.07 \| \| African Caribbeans vs. Europeans:  4.6K vs. 120.4K \| Rate difference: 0.10 \| \| Time from sub-optimal diabetes control to treatment intensification \| South Asians vs. Europeans:  10.5K vs. 120.4K \| HR: 1.04 \| \| African Caribbeans vs. Europeans:  4.6K vs. 120.4K \| HR: 1.04 \| \| Time to antihypertensive initiation \| South Asians vs. Europeans:  7.6K vs. 119.4K \| HR: 1.02 \| \| African Caribbeans vs. Europeans:  3.8K vs. 119.4K \| HR: 1.02 \| \| Proportions of eligible people at high recorded CVD risk receiving statins \| South Asians vs. Europeans:  3K vs. 49K \| HR: 1.15 \| \| African Caribbeans vs. Europeans:  2K vs. 49K \| HR: 1.18 \|   Antihypertensive analyses  Sample sizes as per “feasibility counts” section. Little prior data exists in this area, but we can assume a mean time to measurement of 1 month (with an assumed SD of 1 month), as per guidelines for re-measurement after intensification (24). This would give a detectable ethnic difference in time until first monitoring as 0.04 months for South Asians vs. Europeans (using the power twomeans command in Stata), and 0.06 months for African Caribbeans vs. Europeans. Data from Petersen et al (25) suggest that 21% of those eligible for treatment for hypertension in the UK remain untreated. Adding this proportion to the expected numbers commencing antihypertensives by ethnicity (see feasibility count section), we would expect 119.4K Europeans, 7.6K South Asians and 3.8K African Caribbeans to be eligible for time to antihypertensive initiation analyses.  Lipid-lowering medication analyses  Sample sizes as per “feasibility counts” section. Assuming a mean time to monitoring of 3 months (26) and an SD of 1 month, the detectable ethnic difference in time until first monitoring would be 0.04 months for South Asians vs. Europeans, and 0.06 months for African Caribbeans vs. Europeans (using the power twomeans command in Stata). Chidwick et al reported that 24% of the high risk population received statins (21), equating to detectable ethnic differences in proportions receiving statins of HRs 1.18 and 1.15.  All detectable differences fall below what is likely to be considered clinically significant. |

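### Table 1's second-line sulphonylurea differences (2.0 and 2.9 points) deliver 90% power in one direction only, although the null hypothesis is two-sided; the header also labels power as β

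*Supplement*

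**What the plan says.** The relevant text is in the Supplement, amendment of 9 December 2019.

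- Under Sample size considerations, the Table 1 column header reads "Detectable ethnic difference effect sizes at α=0.05, β=0.90". Each comparison then has a single unsigned figure. The metformin rows give 1.4 ("Difference in proportions: 1.4") and 2.1 points. The sulphonylurea rows give 2.0 and 2.9 points ("Difference in proportions: 2.9").
- The same section takes 73% for first-line metformin and 87% for second-line sulphonylurea from earlier work and names the method ("power twoproportions command"). It does not say which ethnic group carries the baseline, in which direction the difference runs, or whether α is one- or two-sided.
- Feasibility counts supplies the group sizes: "120.4K Europeans, ≈10.5K South Asians and ≈4.6K African Caribbeans initiating first-line treatment", and "34.4K, 3.0K and 1.3K respectively starting second-line treatment".
- The null hypothesis under Objectives, Specific Aims and Rationale has no direction: "No ethnic difference in the proportions of people prescribed metformin as first-line". The same sentence extends to sulphonylureas and the other second- and third-line classes.
- Section N makes European ethnicity the baseline category for every objective.

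**The concern.** For a proportion well above one half, p(1−p) grows as p falls. A gap below an 87% baseline is therefore noisier than the same gap above it and must be larger to be detected with the same power. One unsigned figure can serve a two-sided hypothesis only if it is the larger of the two directional figures. If it is the smaller, the stated power is missed in one of the two directions under test. The effect grows with the size of the gap, so it is largest where the minority group is smallest: 1.3K African Caribbeans on second-line treatment.

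Separately, β conventionally denotes the type II error, so the header taken literally would mean 10% power.

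**Working it through.** **Inputs.** Europeans / South Asians / African Caribbeans: 120,400 / 10,500 / 4,600 (first-line) and 34,400 / 3,000 / 1,300 (second-line). Baselines 0.73 and 0.87. α=0.05, taken as two-sided (an assumption). Target power 0.90.

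**Formula.** Two-proportion test with pooled variance under the null:

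- s0 = √[p̄(1−p̄)(1/nE + 1/nM)], where p̄ is the weighted mean proportion
- s1 = √[pE(1−pE)/nE + pM(1−pM)/nM]
- power = Φ[(|d| − 1.96·s0)/s1]

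**Reproducing the plan's figures.** Difference in points giving 90% power when the second proportion lies above the baseline:

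| Row | Stated | Europeans at baseline, minority higher | Minority at baseline, Europeans higher |
|---|---|---|---|
| Metformin, South Asian | 1.4 | 1.454 | 1.449 |
| Metformin, African Caribbean | 2.1 | 2.139 | 2.128 |
| Sulphonylurea, South Asian | 2.0 | 2.016 | 1.991 |
| Sulphonylurea, African Caribbean | 2.9 | 2.949 | 2.890 |

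The last column rounds to the stated figure in all four rows. The European-baseline column does so in three; the first row fits only if truncated.

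**The other direction.** Difference needed for 90% power when the second proportion lies below the baseline, and power at the stated difference:

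| Row | Europeans at baseline, minority lower | Minority at baseline, Europeans lower |
|---|---|---|
| Metformin, South Asian | 1.47 needed; 86.9% | 1.48 needed; 86.6% |
| Metformin, African Caribbean | 2.18 needed; 87.7% | 2.19 needed; 87.4% |
| Sulphonylurea, South Asian | 2.13 needed; 86.2% | 2.16 needed; 85.2% |
| Sulphonylurea, African Caribbean | 3.20 needed; 84.2% | 3.26 needed; 82.2% |

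**One row in full: sulphonylurea, African Caribbean, d=0.029, Europeans at 0.87.**

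- Decrease: pM=0.841, p̄=0.86894, s0=0.009535, s1=0.010303. (0.029 − 1.96×0.009535)/0.010303 = 1.001, so power is 84.2%.
- Increase: pM=0.899, p̄=0.87106, s0=0.009469, s1=0.008552. (0.029 − 1.96×0.009469)/0.008552 = 1.221, so power is 88.9%.
- The gap comes from s1: 0.841×0.159 = 0.134 against 0.899×0.101 = 0.091.

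**How much is rounding?** With Europeans at baseline, an increase of the stated size has 87.7%, 88.9%, 89.5% and 88.9% power in row order, so rounding alone already costs something. At the top of each rounding interval (1.45, 2.15, 2.05 and 2.95 points) a decrease has 89.0%, 89.1%, 87.8% and 85.3%. For metformin the directional part is about one percentage point of power. For sulphonylurea, 2.13 and 3.20 cannot round to 2.0 and 2.9.

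**Sensitivity to method.** With Europeans at baseline, power for a decrease across the four rows is 84.2-87.8% with a likelihood-ratio test, 83.2-87.4% with continuity correction and 80.4-86.9% with unpooled variance. A one-sided α would give 90.2-92.9%, but its detectable differences do not match the table.

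**The case against.** The strongest reply is that this precision exceeds the inputs. The counts are approximate: they apply an assumed 50% ethnicity recording to census proportions, and the plan calls them conservative because minority groups are over-represented among people with diabetes. With Europeans held fixed and at baseline, minority groups of 11,750, 4,983, 3,439 and 1,586, about 12%, 8%, 15% and 22% above those assumed, would restore 90% power for a decrease of the stated size. The planned analysis is adjusted logistic regression, so a crude two-proportion figure is only indicative. The cohort size is fixed by the database, and Table 1 sets no recruitment target or decision rule. All of this stands, and it keeps the point minor. It does not make the table right on the inputs it states.

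Three stronger readings are tempting and not supported:

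- A reader might infer that the table assumes a minority proportion above the European one, so that a minority deficit is the neglected direction. The documents do not assign the 73% and 87% to a group. The layout that reproduces all four rows by ordinary rounding has the minority at baseline and Europeans higher; there a sulphonylurea deficit of the stated size has about 90.2% power in both rows. Section N, and the fact that Europeans make up 34.4K of about 40K, make a European baseline the natural one, but that is a reason to state it, not evidence of what was computed.
- A reader might extend the directional fault to metformin. Most of that shortfall is rounding.
- A reader might take the header to mean 10% power. The rows reproduce only with power of 0.90, so this is a notation slip.

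**Conclusion.** The point holds as a minor correction. The two sulphonylurea figures overstate power in one of the two directions under test, whichever group carries the baseline: about 86% and 84% with Europeans at 87%, or about 85% and 82% with the minority group at 87%. With Europeans as baseline, the understatement is about 0.13 points (2.13 against 2.0) and 0.30 points (3.20 against 2.9).

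This rests on a two-sided 5% test, the pooled-variance method and the group sizes as stated. Nothing here disturbs the plan's conclusion on clinical significance, since no threshold is given that lies between the stated and the corrected figures.

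**What to change.** In Table 1, replace the four differences with the value detectable in either direction at 90% power with Europeans as baseline, rounded up: 1.5, 2.2, 2.2 and 3.2 points. At these values a decrease has 90.9%, 90.4%, 91.6% and 90.0% power, and an increase has more. State the baseline group and the two-sided α beside the table. The baseline group matters because 3.2 points with the minority group at 87% and Europeans lower gives only 88.9%. Relabel the header as power 0.90 (β=0.10).

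The cost is five cells and one sentence, with figures slightly less favourable than now. Design, data and analysis stay as they are.

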| N. Exposures, outcomes and covariates *Data sources are listed in square parentheses*  Exposures:  For all objectives, the exposure is either South Asian or African Caribbean ethnicity (defined as above), with European ethnicity as the baseline category. *[Primary care clinical records]*  Health Outcomes by study objective:   1. Proportion of those eligible for primary prevention who are prescribed a) antihypertensives and b) lipid-lowering medication *[Primary care clinical records, prescription drug files]* 2. Time to first anti-diabetic/ antihypertensive/ lipid-lowering medication prescription. *[Primary care clinical records, prescription drug files.]* 3. Choice of a) anti-diabetic (first- to third-line), b) antihypertensive and c) lipid-lowering medications, see appendix for code lists for each (derived from chapters of the British National Formulary). *[Prescription drug files.]* 4. Doses used for each a) anti-diabetic, b) antihypertensive and c) lipid-lowering medication. *[Prescription drug files.]* 5. Monitoring rate, stratified by the time since treatment initiation, e.g. the number of a) HbA1c, b) BP or c) lipid measures divided by the amount of person time, within strata of time since initiation (i.e. first year, second year since initiation etc). *[Prescription drug files, test records.]* 6. Time to treatment intensification after detection of sub-optimal risk factor control. *[Primary care clinical records, prescription drug files, test records.]* Sub-optimal control will be classified as follows:    1. Diabetes; HbA1c≥53mmol/mol (7.5%) (7)    2. Hypertension; blood pressure≥140/80 mmHg, or 130/80 mmHg in those with neuropathy/ nephropathy or retinopathy (24)    3. Lipids; <40% reduction in non-HDL cholesterol (25) 7. Influence of the following on associations between ethnicity and prescribing: smoking, BMI, deprivation, polypharmacy, multi-morbidity, drug adherence (for outcomes iv) and v)), patient engagement with healthcare, diabetes duration and HbA1c. *[Linked IMD data, primary care clinical records, prescription drug files, test records.]*   Covariates (all taken from last entry in medical notes prior to follow-up time commencing)  Age *[Primary care clinical records]*  Sex *[Primary care clinical records]*  Smoking status *[Primary care clinical records]*  BMI *[Primary care clinical records]*  Deprivation (using patient-level IMD scores, with sensitivity analyses using practice-level IMD scores) *[Primary care clinical records, linked deprivation data]*  Polypharmacy (number of medications) *[Prescription drug files]*  Multimorbidity (defined by presence or absence of the following key co-morbidities: coronary heart disease, cerebrovascular disease, heart failure, atrial fibrilliation, hypertension, chronic kidney disease, peripheral arterial disease, retinopathy, neuropathy, cancer [any], COPD/ asthma, severe mental illness) *[Primary care clinical records]*  Patient engagement/ access (using the number of consultations in the year preceding diabetes diagnosis as a proxy) *[Primary care clinical records]*  Patient adherence (using the proportion of days covered: PDC=days of medication supplied per x day period/ x (27)). This will be calculated separately for all medications issued over the follow-up time of interest, and then a mean PDC for all medications will be derived for each patient. Both measures are important as adherence may vary by drug. *[Prescription drug files]*  Disease parameters: baseline HbA1c/ blood pressure and number of years since diabetes diagnosis *[Primary care clinical records, test records.]* |

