| O. Data/ Statistical Analysis For all parts of the study, the population will be people with and without new-onset type 2 diabetes active in CPRD from 2006 (see section K, above) and the exposure will be ethnicity (either South Asian vs. European [baseline] or African Caribbean vs. European [baseline], as detailed in section L, above). Covariates in base models will include age and sex, and further covariates will be considered individually, as outlined in section vi) below. Statistical analysis is further considered by objective:   1. **Outcome:** Proportion of those eligible for primary prevention who are prescribed a) antihypertensives and b) lipid-lowering medication   **Entry:** Date of incident a) hypertension Read code/ raised BP reading or b) elevated 10 year CVD risk score, at least 12 months after study start date of 1^st^ January 2005  **Exit:** First of; date of first antihypertensive/ lipid-lowering medication prescription (defined by the absence of a prescription for the medication in the previous 6 months’ records), end of study, leaving CPRD practice or death  **Analysis:** Proportions receiving antihypertensives/ statin will be compared by ethnicity, then logistic regression models will be used to adjust for confounding/ investigate potential mediators  **Example effect measure:** Odds ratio (OR) of receiving an antihypertensive/ lipid-lowering medication vs. not for each ethnic group of interest, stratified by time period since identification of hypertension/ elevated CVD risk   1. **Outcome**: time to initiation of first-line anti-diabetic/ antihypertensive/ statin, probability of receiving anti-diabetic/ antihypertensive/ statin at one year post-diagnosis/ identification of high CVD risk   **Entry**: date of type 2 diabetes diagnosis/ incident hypertension Read code or raised BP reading/ incident high 10 year CVD risk score recording  **Exit**: date of first anti-diabetic/ antihypertensive/ statin prescription (defined by the absence of a prescription for the medication in the previous 6 months’ records), or end of study/ leaving CPRD practice/ death  **Analysis**: summary statistics will be compared by ethnicity using Kaplan-Meier time-to-event analysis (cumulative failure probability in a given time frame by ethnicity, comparison of medians by log-rank test), Cox proportional hazards regression models will be used to adjust for confounding/ investigate potential mediators  **Example effect measure**: hazards ratio (HR) for anti-diabetic/ antihypertensive/ statin prescription   1. **Outcome:** proportions of patients prescribed medication from each anti-diabetic (stratified by first- to third-line treatment), antihypertensive and lipid-lowering class (defined by the absence of a prescription for the medication in the previous 6 months’ records)   **Sub-population:** a) all participants starting first- to third-line anti-diabetic treatment, b) all patients on antihypertensives, or c) all patients on lipid-lowering medication  **Analysis:** proportions receiving each drug will be compared by ethnicity, then logistic regression models will be used to adjust for confounding/ investigate potential mediators  **Example effect measures**: odds ratio (OR) of being prescribed metformin (=1) vs. non-metformin medication (=0) at first stage of treatment, OR of being prescribed sulphonylurea (=1) vs. non- sulphonylurea medication (=0) at second stage of treatment, OR of calcium-channel blocking antihypertensive prescription vs. non- calcium-channel blocking antihypertensive in those on antihypertensive treatment, OR of statin prescription vs. non-statin lipid-lowering medication prescription in those with >10% 10 year cardiovascular risk   1. **Outcome:** proportions of patients prescribed each dose of each anti-diabetic, antihypertensive and lipid-lowering medication, stratified by treatment stage (defined by the absence of a prescription for the medication in the previous 6 months’ records)   **Sub-population:** a) all participants on first- to third-line anti-diabetic treatment, b) all patients on antihypertensives, or c) all patients on lipid-lowering medication  **Analysis: :** proportions receiving each dose of each drug will be compared by ethnicity, then logistic regression models will be used to adjust for confounding/ investigate potential mediators  **Example effect measures**: OR of being prescribed maximum dose (2g daily) vs. sub-maximum dose of metformin, OR of being prescribed atorvastatin 10mg per day vs. higher doses (20mg, 40mg or 80mg)   1. **Outcome:** yearly monitoring rate post commencement of medication from each anti-diabetic (first- to third-line), antihypertensive and lipid-lowering class – i.e. number of times HbA1c/ blood pressure/ blood lipids measured per person-year of follow-up, stratified by year after commencement; may be multiple entry dates per person for different medications   **Entry:** first use of any medications of interest from 2006 onwards  **Exit:** first of; end of strata (e.g. 1 year after medication commencement), end of study/ leaving CPRD practice/ death  **Analysis:** summary statistics will be compared by ethnicity, Poisson regression modelling used to adjust for confounding/ investigate potential mediators  **Example effect measures**: yearly monitoring rate ratios (RRs)   1. **Outcome:** time to medication intensification (up-titration, addition or switching) after detection of sub-optimal control of diabetes, hypertension or blood lipids, or probability of intensification 1 year post-detection of sub-optimal control; may be multiple entry dates per person for different medications   **Entry:** date when sub-optimal risk factor control detected (see section M for how this is defined for each risk factor)  **Exit:** first of; date of anti-diabetic, antihypertensive or lipid-lowering treatment intensification, end of study/ leaving CPRD practice/ death  **Analysis:** summary statistics will be compared by ethnicity using Kaplan-Meier time-to-event analysis (cumulative failure probability in a given time frame by ethnicity, comparison by log-rank test), Cox proportional hazards regression models will be used to adjust for confounding/ investigate potential mediators  **Example effect measures**: cumulative failure probability for each ethnic group 1 year post detection of sub-optimal value, comparison of median survival times using the log-rank test by ethnicity, HRs of intensification stratified by year   1. **Outcome:** influence of deprivation, polypharmacy, multi-morbidity, drug adherence (iv) and v) only), patient engagement with healthcare, diabetes duration and HbA1c on any ethnic differences found in i) to v).   **Entry:** as above for i), iv) and v)  **Exit:** as above for i), iv) and v)  **Analysis:** as above for i) to v)  **Covariates:** smoking status, BMI, deprivation, polypharmacy, multi-morbidity, drug adherence, patient engagement with healthcare, diabetes duration and HbA1c  **Effect measures:** we will observe the degree of attenuation of the ethnic difference effect measure for each outcome when each covariate is inserted in turn to models, and thus evaluate the likelihood of confounding or mediation  Sub-group/ sensitivity analyses  See section O of original application  Plans for addressing misclassification and bias  See section O of original application  Multiple comparisons  See section O of original application |

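### The precision stated for blood-pressure and lipid monitoring is for time to first check, which the plan does not analyse; the planned monitoring outcome is a yearly measurement rate

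*Supplement*

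**What the plan says.** All references are to the amendment of 9 December 2019 in the Supplement.

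- **Sample size considerations, antihypertensives:** "we can assume a mean time to measurement of 1 month (with an assumed SD of 1 month", which the plan takes from guidance on re-measurement after intensification. The result is: "This would give a detectable ethnic difference in time until first monitoring as 0.04 months for South Asians vs. Europeans", with 0.06 months for African Caribbeans.
- **Sample size considerations, lipids:** "Assuming a mean time to monitoring of 3 months (26) and an SD of 1 month", again giving 0.04 and 0.06 months.
- **Same section, closing sentence:** "All detectable differences fall below what is likely to be considered clinically significant".
- **Section N, outcome 5:** monitoring is a count of measures over person-time, "within strata of time since initiation (i.e. first year, second year since initiation etc".
- **Section O, monitoring analysis:** the outcome is the "number of times HbA1c/ blood pressure/ blood lipids measured per person-year of follow-up, stratified by year after commencement", modelled by Poisson regression, with yearly rate ratios as the effect measure.
- **Section D and the objectives:** the time outcomes are time to first prescription and time to intensification. The monitoring objective and its null hypothesis concern rates.
- **Anti-diabetic drugs, by contrast:** precision is given on the rate scale (mean 2.45 per year, SD 2; detectable differences 0.07 and 0.10 per person-year), which matches the planned outcome.

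**The concern.** A detectable difference tells the reader what a study can resolve on the outcome it will report. Here the blood-pressure and lipid figures are for a mean time in months, while the results will be rate ratios of yearly counts. Neither can be derived from the other without assumptions that the plan does not state. The reader therefore has no precision statement for two of the three monitoring comparisons, although the closing sentence covers all of them.

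There is also a gap in what is measured. The intensification analysis starts its clock when sub-optimal control is detected, so any wait between starting a drug and the first check lies before that clock starts. The monitoring analysis covers this period but only counts measurements within it. If ethnic groups differed in how soon the first check came but not in how many checks were made in the year, no planned estimate would show it. A rate ratio near 1 could then be read as equal monitoring in every respect.

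**Working it through.** **Inputs.** Alpha 0.05, taken as two-sided, and power 0.90, from the Table 1 header "Detectable ethnic difference effect sizes at α=0.05, β=0.90" (the 0.90 is read as power). The antihypertensive and lipid paragraphs give no values of their own, so the same are assumed. Numbers come from Feasibility counts, people with diabetes: antihypertensives 92.7K European, 8.1K South Asian, 3.5K African Caribbean; lipids 77.1K, 6.7K and 2.9K.

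**Formula (two means, unequal groups).** Detectable difference = (1.960 + 1.282) × SD × √(1/n₁ + 1/n₀).

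**Step 1: reproduce the plan's figures, SD 1 month.**

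| Comparison with Europeans | √(1/n₁ + 1/n₀) | Result (months) | Stated |
|---|---|---|---|
| Antihypertensive, South Asian | 0.01159 | 0.0376 | 0.04 |
| Antihypertensive, African Caribbean | 0.01722 | 0.0558 | 0.06 |
| Lipid, South Asian | 0.01274 | 0.0413 | 0.04 |
| Lipid, African Caribbean | 0.01892 | 0.0613 | 0.06 |

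All four agree. At 80% power the African Caribbean values would be 0.048 and 0.053, which round to 0.05, so 90% two-sided is the setting that fits. The same formula with SD 2 per year gives 0.066 and 0.097 for HbA1c monitoring, against the stated 0.07 and 0.10.

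**Step 2: look for the outcome.** Time to first monitoring does not appear in section D, the objectives, the null hypotheses, section N or section O.

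**Step 3: precision on the planned scale.** The documents give no mean or SD for blood-pressure or lipid measurement rates, so these are illustrations. Detectable rate difference per person-year, diabetes cohort:

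| Assumed SD per year | BP, South Asian | BP, African Caribbean | Lipid, South Asian | Lipid, African Caribbean |
|---|---|---|---|---|
| 1 | 0.038 | 0.056 | 0.041 | 0.061 |
| 2 (the plan's HbA1c value) | 0.075 | 0.112 | 0.083 | 0.123 |
| 3 | 0.113 | 0.167 | 0.124 | 0.184 |
| 4 | 0.150 | 0.223 | 0.165 | 0.245 |

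As a rate ratio, exp[3.242 × √(φ/(λn₁) + φ/(λn₀))], with λ measurements per year, one person-year each and variance φ times the mean: for λ from 1 to 4 and φ from 1 to 2, about 1.02 to 1.06 (South Asian) and 1.03 to 1.09 (African Caribbean).

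**Step 4: people without diabetes.** The stated month figures reproduce from the diabetes-cohort numbers, but the amendment adds a second population.
- Antihypertensives, 94K, 6K and 3K: with SD 2 per year, 0.086 and 0.120.
- Lipids, 49K, 3K and 2K: 0.122 and 0.148. These counts are people with a high recorded risk score. The plan cites 24% of such people as receiving statins. If only they enter the analysis, dividing by √0.24 = 0.490 gives about 0.25 and 0.30.

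**Step 5: what the yearly count registers.** Checks at months 1 and 12, or at months 10 and 12, both give two in the first year, so that delay leaves the rate unchanged. Checks at months 1, 6 and 12 against months 10 and 12 give three and two, so that delay does show, though as a lower count and not as a time.

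**The case against.** The case for the plan is substantial. These are existing records, so no recruitment target depends on the figures, and on any reasonable assumption the rate-scale precision in the diabetes cohort is good. The study asks about monitoring frequency: its background, objective and null hypothesis all say so, and a null rate ratio would answer that hypothesis. The base application also puts clinically meaningful effect sizes ahead of p values. Time to first check would be a new outcome, and its link to later intensification is plausible but not quantified.

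Most of this stands, and it rules out several stronger readings:

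- **That a late first check goes wholly unseen.** A delay that reduces the first-year count would partly show in the first-year stratum.
- **That the study is underpowered, or the clinical-significance sentence false.** The calculations suggest neither; the sentence is simply not shown for these rates.
- **That the plan undertakes to test checks against guideline windows.** It uses 1 and 3 months only as assumed means, and cites the 1-month value for re-measurement after intensification, whereas the planned rate starts at commencement.
- **That the 0.04 and 0.06 figures could serve a new time-to-event analysis.** They are differences in uncensored means, not hazard ratios, and reproduce from the diabetes-cohort numbers.

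The mismatch itself remains. If frequency is the question, the precision paragraph describes the wrong outcome; if timeliness is the question, the outcome list lacks it.

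**Conclusion.** The point holds as a mismatch between the stated precision and the planned outcome, confined to blood-pressure and lipid monitoring. The 0.04 and 0.06 month figures are arithmetically right but belong to an outcome that is not analysed, so the closing claim is unsupported for those two rates. Timing of the first check is not estimated, and a delay is visible only through a lower yearly count.

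The practical effect on power is probably modest: in the diabetes cohort, about 0.075 to 0.18 measurements per year with an SD of 2 to 3. That range rests on borrowed or assumed SDs, two-sided 0.05, 90% power and the feasibility counts. It is wider for lipids in people without diabetes. The point merits correction but does not threaten the study.

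**What to change.** 1. In Sample size considerations, replace the month figures with detectable differences or rate ratios for yearly blood-pressure and lipid measurement rates. State the assumed rate, the SD or overdispersion, alpha and power. If the HbA1c SD of 2 is borrowed, say so.
2. Give these separately for people with and without diabetes, using the numbers on treatment for lipids.
3. Limit the closing sentence to outcomes for which a figure is given.
4. If timeliness is of interest, as the present calculation implies, add a secondary monitoring outcome: time from medication commencement to the first subsequent blood-pressure or lipid measurement. Analyse it by Kaplan-Meier and Cox, with exit at first measurement, end of study, leaving the practice or death, and state its precision as a hazard ratio.

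Items 1 to 3 cost only wording and a short calculation. Item 4 uses prescription and test dates already needed for other objectives. It adds comparisons in each drug group (two ethnic contrasts, more if split by class or cohort), to which the existing multiple-comparisons statement would apply. If frequency alone is intended, item 4 can be omitted, with a sentence saying that timing is not assessed.
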